### Data sources

The study will use non-identifiable data from three EPaCCS across three distinct geographical locations in the UK, namely London, Leeds and Bradford, which combined have a population of 10.4 million people. These EPaCCS were introduced at different times within the same city and across different cities. This has led to natural variation in exposure, resulting in datasets that cover varying time periods: 2010–2022 in London, and 2015–2023 in Leeds and Bradford. Nonetheless, these EPaCCS are well established and contain a sufficient number of records, as illustrated in table 1, to enable meaningful individual site analyses and answer our research questions. Additional anonymised EPaCCS data from different regions will be considered if made available during the study. The sample size will be determined by the data available in the three datasets and will vary depending on the analysis.

**Table 1 T1:** EPaCCS and data availability

EPaCCS location	EPaCCS specific data
London EPaCCS	Coordinate My Care (CMC) served as the commissioned EPaCCS in London from 2010 to 2022, during which time it was also the largest UK EPaCCS. Covering 32 CCGs serving a population of 8.9 million, this EPaCCS dataset reflects a diverse urban patient population in terms of diagnosis, ethnicity and socioeconomic background. CMC records comprise data from various healthcare settings, including primary and secondary care, hospices and nursing homes. The dataset encompasses demographics, diagnoses, care preferences, the ceiling of treatment, resuscitation status, living circumstances, prognosis, performance status, date and place of death. Additionally, data is available regarding how often the record was accessed by urgent and non-urgent healthcare workers. In later years, patients had the option of starting a ‘MyCMC’ plan, whereby they use a patient portal to input some data themselves. The anticipated numbers for inclusion in the dataset are 140 000 records, of which 100 000 are for deceased patients.

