North West London dataset	CMC records will be linked with the ‘Whole Systems Integrated Care’ (WSIC) dataset. WSIC is an electronic record used by healthcare professionals in North West London, which has a population of 2.4 million, to document essential information about patient care in the region (eight health boroughs, previously defined as CCGs).^65^ The WSIC dataset will include all individuals who have died in North West London within the timeframe spanning from 2010 to 2023. This linkage will allow the creation of two cohorts for comparison: individuals with EPaCCS (CMC) and those without EPaCCS. All decedents with a CMC record within the WSIC catchment area will be identified for inclusion within the linked dataset, while decedents without such records will form the control group. The WSIC dataset includes coded primary, secondary, acute, mental health, community health and social care data. This dataset also includes detailed information on social determinants of health, including ethnicity, and mortality data, including place of death. Cost data is also available as patient-level costs referring to the indicative spend calculated separately for each patient for each healthcare sector. This will be used in a cost minimisation analysis of EPaCCS, and it includes primary care level, acute, community, mental health and social care costs. Data linkage will be carried out by North West London Integrated Care Board and supported by existing data sharing framework.^66^ Figure 1 illustrates the data flow and linkage process. The linked dataset will be de-identified prior to being made available to the research team for the analysis

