### Analysis

The data from each of the three distinct EPaCCS will be analysed separately. Individual patient-level EPaCCS data will be accessed and cleaned for each of the three systems. The study will categorise the data into social determinants of health (age, gender, ethnicity, social deprivation), clinical characteristics and elements relating to ACP. The social determinants of health have been identified from existing literature for being associated with poor health experiences and outcomes. The study will assess the completeness of variables in the data, examining patterns of missing data at the individual level and identifying any outlier records. Based on the characteristics of missing data, the study will adopt an appropriate approach to treating missing data for statistical analysis. Several methods will be considered that are appropriate for missing at random and not missing at random data. Though, it is assumed that the missing mechanism will be missing not at random. However, no robust methods of imputing missingness in the independent variables with a missing not at random mechanism have been identified. If imputation was carried out, a sensitivity analysis will be conducted to compare parameter estimates with/without imputation. Missing values for key outcomes will be imputed using gender, age, comorbidity, cause of death, IMD and/or study area.^45^ For each ACP element, documented decisions will be categorised to create an outcome (binary or ordinal) variable for inclusion in logistic regression modelling of the relationship between each of these outcomes, as distinct analyses, and social determinants of health, adjusting for major confounding variables and consideration of random effects/fixed effects (eg, comorbidity). Confounders will be selected using expert knowledge, existing literature, and the completeness and availability of the data. Using the London and Leeds datasets, a dichotomised binary outcome of whether or not a patient has an EPaCCS record will be created for logistic regression, modelling the association between the creation of EPaCCS records and social determinants of health. The study will identify both similarities and differences between the creation, use and content of EPaCCS records in the three EPaCCS cohorts. Mindful of the reported challenges associated with the interoperability of EPaCCS data,^46^ the comparison of datasets will be cautiously approached. We will examine the impact of the significant increase in EPaCCS records in London,^47^ and potentially the two other cities, following the outbreak of COVID-19 in March 2020 in terms of the documentation and completeness of ACP elements within the EPaCCS records. We will carry out a secondary analysis (sensitivity analysis) excluding individuals whose records were created during the COVID-19 pandemic after examining the data and the trend in the creation of EPaCCS records.

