### Sensitivity analysis

We will consider a number of approaches in terms of sensitivity analyses, which will be informed by the availability and completeness of the data.^57^ Sensitivity analyses will be conducted on the cohort identification strategy and our choice of covariates used for estimating the propensity scores.^58^ We will also consider several approaches and sensitivity analysis techniques to deal with unobserved confounding, the implementation of new policies and the effect of the COVID-19 pandemic on both the intervention and the outcomes of interest.^33 59^ In terms of the COVID-19 pandemic, we will build on our previous evaluation,^47^ identify the records created during the pandemic and, if appropriate, perform a sensitivity analysis by potentially excluding these records to assess the impact of this period on our findings.

### Outputs from work package 2

The second work package will provide novel insight into the effect and value of EPaCCS and ACP on end-of-life care quality outcome measures. We will derive high-quality evidence on how the intervention affects costs in a context where a trial is unfeasible. Secondary analysis will provide insights into how end-of-life care interventions may address or exacerbate inequities in the context of systematic gaps.

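### In the North West London comparison, deaths after CMC closed enter as controls who could no longer obtain a record, and the COVID-19 exclusion by record-creation date can remove only record-holders

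*Protocol article*

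**What the plan says.** All references are to the protocol article.

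- **Exposure period** (Data sources, Table 1, London EPaCCS): "Coordinate My Care (CMC) served as the commissioned EPaCCS in London from 2010 to 2022".
- **Death file** (Table 1, North West London dataset): "The WSIC dataset will include all individuals who have died in North West London within the timeframe spanning from 2010 to 2023".
- **Groups** (same entry): anyone in the catchment who died and had a CMC record counts as a record-holder. For the rest, the rule is that "decedents without such records will form the control group". Neither group is limited by date of death.
- **Use** (Table 2): the linked file serves 1E, 2A and 2B. It is the only source for 2B, and the ecological analysis is confined to North West London. Leeds contributes to 1E and 2A with deaths in 2021–2023 for both groups.
- **COVID-19, work package 1** (Analysis): a planned sensitivity analysis "excluding individuals whose records were created during the COVID-19 pandemic".
- **COVID-19, work package 2** (Sensitivity analysis): a conditional plan to "perform a sensitivity analysis by potentially excluding these records".
- **Adjustment for time**: the individual-level outcome model includes season or financial quarter. The factors given as examples for the propensity score are age, sex, ethnicity, deprivation and primary diagnosis; calendar time is not among them.

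**The concern.** Inverse probability weighting needs every person in the comparison to have had some chance of holding a record. Once CMC closed, someone without an earlier record had none. Such people are controls because of when they died. If hospital deaths, bed days or costs in that period differ from earlier years, the difference enters the control mean and may be read as an effect of EPaCCS. In the ecological analysis, the measured share of deaths with a record falls after closure because the register stopped, whatever happened to care planning.

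The COVID-19 rule has a different fault. Controls have no record-creation date, so the rule cannot apply to them. In 2A and 2B it would thin the pandemic period on one side only. In 1E, holding a record is the outcome, so the rule deletes people because of their outcome. If pandemic uptake differed by deprivation or ethnicity, the sensitivity analysis would show an inequality that it had created itself.

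**Working it through.** The article gives no figure to reproduce: sample size follows from the available data, and no uptake is stated for North West London. The dates can be compared directly. The sizes below are illustrations on stated assumptions.

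**1. Dates.** CMC: 2010–2022. Deaths: 2010–2023, which is 14 calendar years. One year, 2023, lies wholly after CMC's stated end. The month of closure is not given, so part of 2022 may belong there too.

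**2. Share of controls from 2023.** Assume equal deaths per year, uptake *u* in each of the 13 CMC years, and no record-holders dying in 2023. Then *f* = 1 / (1 + 13(1 − *u*)). If the hospital-death rate in 2023 differs from that in other years by *d* points, the control rate shifts by *f* × *d*.

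| *u* | *f* | shift, *d* = 5 | shift, *d* = 10 |
|---|---|---|---|
| 10% | 1/12.7 = 7.9% | 0.39 | 0.79 |
| 25% | 1/10.75 = 9.3% | 0.47 | 0.93 |
| 50% | 1/7.5 = 13.3% | 0.67 | 1.33 |

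The hypothesised hospital-death rates (Creating comparative cohorts) are 22–30% with EPaCCS and 45–50% without, a difference of 45 − 30 = 15 to 50 − 22 = 28 points.

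**3. Adding a COVID-19 exclusion of record-holders only.** As an extreme case, take a two-year exclusion in which records are created and deaths occur in the same period. Controls from years without comparable record-holders are then *f* = (1 + 2(1 − *u*)) / (1 + 13(1 − *u*)):

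- *u* = 10%: 2.8/12.7 = 22%
- *u* = 25%: 2.5/10.75 = 23%
- *u* = 50%: 2/7.5 = 27%

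The shift is 1.1–1.3 points at *d* = 5 and 2.2–2.7 points at *d* = 10.

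**4. The COVID-19 rule in 1E.** Take two social groups with the same true coverage, 50%. Suppose 50% of records in group A and 30% in group B were created in the pandemic. After the exclusion:

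- A: 0.25 with a record, 0.50 without; odds 0.50
- B: 0.35 with a record, 0.50 without; odds 0.70
- Odds ratio = 0.50/0.70 = 0.71, where the truth is 1.00

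**5. Ecological slope.** Assume true coverage rises linearly from 0 to 40% over 2010–2022 and stays at 40% in 2023, with a true slope of −0.20 and no other trend. The fitted slope is −0.20 × Sxt/Sxx, where x is recorded and t is true coverage.

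- 2023 recorded as 0%: Sxt = 0.165, Sxx = 0.239, ratio 0.69, slope −0.14
- 2023 recorded at 30% of true (12%): Sxt = 0.187, Sxx = 0.208, ratio 0.90, slope −0.18

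This holds only if EPaCCS-type planning continued unrecorded after CMC, which the article does not say.

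**6. Does the planned adjustment cover this?** If the time term means season, it does not adjust for year. If it means quarter within year, it adjusts the outcome model for calendar time. On neither reading does it supply newly exposed comparators after closure.

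**The case against.** Several points on the other side stand.

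- A reader might infer that record-holders and controls come from different calendar windows. They do not. Both come from one 2010–2023 death file and overlap throughout 2010–2022. What differs is the opportunity to obtain a record.
- Deaths in 2023 need not all be controls. Table 1 expects "140 000 records, of which 100 000 are for deceased patients", so 140 000 − 100 000 = 40 000 London records are for people not recorded as deceased. Those who died in North West London in 2023 still count as exposed. The zero-coverage assumption in steps 2 and 5 is therefore an upper case.
- The article leaves room for correction. It will consider other ecological approaches after seeing annual numbers, plans sensitivity analyses on cohort identification, and will consider further approaches to COVID-19. None of these states a common window or a rule for controls.
- The work package 1 exclusion follows a sentence about completeness of ACP elements, so it may be meant for record-holders only, where it is coherent. But the same section also sets out the 1E model, and the exclusion is not limited to other objectives. The work package 2 version is conditional, and no primary estimate depends on either.
- A reader might also want deaths before CMC reached each borough removed, or might suspect misclassification by a successor system. The article gives no borough start dates and mentions no successor, and it treats staggered introduction as the natural variation in exposure that the design uses.

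The full analysis plan may define cohort dates. Even so, the article itself fixes the death window, the control definition and the creation-date rule, and these do not fit together for 1E, 2A and 2B.

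**Conclusion.** The point holds for North West London. Deaths after CMC closure without an earlier record enter as controls with no remaining route to exposure, and a creation-date COVID-19 exclusion is not a valid robustness check in 1E, 2A or 2B.

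The 2023 problem is modest: about 8–13% of controls and a shift of 0.4–1.3 points, or 1.1–2.7 points with the one-sided COVID-19 exclusion in its extreme form. These figures rest on assumed uptake of 10–50%, equal yearly deaths, no record-holders dying in 2023, and an assumed 5–10 point difference in hospital-death rate whose sign is unknown. A reader might infer that the calendar could account for the whole expected effect; against a hypothesised 15–28 points, it could not. No size is derived for costs.

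The 1E figure of 0.71 is exact arithmetic on assumed inputs. It shows that the rule can create an apparent inequality; nothing calculated here shows it reversing a real one. The window mismatch does not arise in Leeds, but the one-sided exclusion would affect Leeds too if applied to the comparison there.

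**What to change.** 1. For 1E, 2A and 2B in North West London, end the date-of-death window at CMC closure for both groups, state the closure date, and drop later borough-years from the ecological analysis.
2. Include calendar time (year and quarter of death) in both the propensity and the outcome models.
3. For 1E, 2A and 2B, define any COVID-19 exclusion by one date-of-death window applied equally to decedents with and without records. Keep the creation-date rule only for analyses confined to record-holders.

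This takes a few lines in the analysis plan and no new data. The cost is the loss of post-closure deaths, about one year in 14 (7% if deaths are even), including those of earlier record-holders. Whether also to restrict by borough start date is a separate trade-off, because it would give up variation that the natural experiment relies on.

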### Work package 2: evaluation of the effect of EPaCCS on place of death and secondary healthcare use at end of life and cost minimisation analysis of EPaCCS (objectives 2A and 2B)

The second work package will adopt a retrospective cohort design under a natural experiment framework to evaluate the effects of EPaCCS on quality indicators of end-of-life care. The quality indicators used in this work package include the place of death (primary outcome) and time spent in hospital in the last 90 days of life (secondary outcome).^48^ The hypothesis for work package 2 is that people with EPaCCS records are less likely to die in hospital and more likely to spend less time in hospital in the last 90 days of life compared with people without EPaCCS records. An EPaCCS record may address one or both sides of the cost-effectiveness ratio; reducing futile or unwanted treatments will save hospital resources while improving goal-concordant care realises more utility. However, there is also the potential for increased costs, notably through substitution effects, for example, if people die in a hospice instead of in a hospital. We therefore hypothesise that EPaCCS improve the cost-effectiveness of care near the end of life.

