Using the CMC-WSIC linked dataset and the Leeds dataset, the study will use a natural experiment approach^33^ and establish cohorts of patients who have died having EPaCCS (case) or not having an EPaCCS (control) in each dataset separately. Place of death will be coded as a binary variable for individual-level analysis, indicating whether death occurred in a hospital or elsewhere. For ecological analysis, rates of hospital deaths per year will be calculated for each one of the eight health boroughs (previously called CCGs) in North West London. Time spent in hospital will be derived as a continuous variable measuring the number of days between admission and discharge within the last 90 days of life, or between admission and death for patients who died in hospitals. Rates of time spent in hospital within the last 90 days of life per year will also be calculated. The cost analysis will use the patient-level cost data available in WSIC. Formal costs will be estimated by combining utilisation frequencies in the data with unit costs for different services.^49^ Informal care hours will be estimated from the literature on end-of-life care populations and associated costs using the substitution method (primary analysis) and opportunity cost method (sensitivity analysis). Intervention costs will be estimated using NHS data.^50^ We will model costs after diagnostic testing of different modelling approaches in the context of distributional characteristics.^51^

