### Creating comparative cohorts

This study will take an inclusive approach to defining the cohorts for inclusion in the individual-level analysis, identifying deceased patients who had mention of one of the four main disease-related causes of death in their clinical records within the last year of life (cancer, dementia, heart or lung disease). Based on previous analyses^52^ and publicly available national data,^53^ we hypothesise that 22–30% of the EPaCCS cohort will die in the hospital compared with 45–50% in the non-EPaCCS group. The inverse probability of treatment weighting will be used to account for the confounding resulting from the non-random allocation of EPaCCS to the groups and balance characteristics between cohorts.^54^ First, a multivariable logistic regression will be used to determine the propensity score weights. Factors included in the model to estimate propensity scores will include the confounders selected to be included in the main outcome analysis (such as age, sex, ethnicity, deprivation and primary diagnosis). These confounders will be cautiously selected based on thorough discussions with our team, which includes experts in palliative care, input from the patient and public involvement group with lived experience in end-of-life care, and a comprehensive literature search. Then, for each patient inpatient encounter, a weight defined as the inverse of the probability of the treatment they had received will be calculated. The balance of patients’ characteristics will be assessed visually and by examining the standardised mean differences.^55^

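### Objective 2B is labelled a cost-minimisation analysis although work package 2 expects different outcomes and better cost-effectiveness; no joint cost-outcome measure is described, and the article does not show whether hospice care is costed

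*Protocol article*

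**What the plan says.** Table 1 (North West London dataset) describes patient-level indicative spend by sector, to be "used in a cost minimisation analysis of EPaCCS, and it includes primary care level, acute, community, mental health and social care costs". The heading of work package 2 repeats the label: "cost minimisation analysis of EPaCCS (objectives 2A and 2B".

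The text under that heading hypothesises that "people with EPaCCS records are less likely to die in hospital and more likely to spend less time in hospital". It argues that a record may act on either side of the cost-effectiveness ratio, saving hospital resources "while improving goal-concordant care realises more utility". It warns that costs could instead rise through substitution, "for example, if people die in a hospice instead of in a hospital", and then concludes: "We therefore hypothesise that EPaCCS improve the cost-effectiveness of care near the end of life". The section on creating comparative cohorts expects that "22–30% of the EPaCCS cohort will die in the hospital compared with 45–50% in the non-EPaCCS group".

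Table 2 defines 2B as the effect of a record on healthcare costs in the final 90 days, using the linked WSIC-CMC data only. Objective 2A uses the same linked data plus Leeds. The costing text in work package 2 relies on WSIC patient-level costs, utilisation multiplied by unit costs, and an estimate of intervention costs. It also says: "Informal care hours will be estimated from the literature on end-of-life care populations".

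**The concern.** Cost minimisation ranks options by cost alone. That is defensible only if the options give the same outcome, and this work package is built on the expectation that they do not. A cost difference cannot by itself show whether cost-effectiveness improved. If costs rise and hospital deaths fall, which the plan allows for, a cost-minimisation rule goes against EPaCCS even where the extra cost might be judged worthwhile. If costs fall and outcomes worsen, the same rule favours EPaCCS.

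The second matter is coverage of costs. The plan identifies a move from hospital to hospice as the example of how costs could rise, yet the lists of WSIC cost sectors and WSIC coded data do not mention hospice. If hospice use is missing from the totals, the hospital side of that move is counted and the hospice side is not.

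**Working it through.** The article gives no cost figure, unit cost or sample size for 2B, so there is no figure to reproduce. The check is a comparison of the text with two short pieces of algebra.

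**1. Method against hypothesis**

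- Method named: cost minimisation (Table 1 and the work package 2 heading), which requires an outcome difference of zero.
- Outcome expected: fewer hospital deaths and less hospital time. The anticipated rates differ by 45 − 30 = 15 to 50 − 22 = 28 percentage points. These are expected group differences taken from earlier analyses and national data, not adjusted effects; the directional hypothesis alone is enough for the contradiction.
- Economic hypothesis: improved cost-effectiveness.
- Measures described: outcomes in 2A, costs in 2B, no measure joining them.

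Let ΔC be the added cost per decedent with EPaCCS, ΔE the hospital deaths avoided per decedent, and λ the value placed on avoiding one (not given in the article). Cost minimisation favours EPaCCS only if ΔC < 0. A cost-effectiveness rule favours it if λΔE − ΔC > 0. When ΔE > 0 the two rules conflict wherever 0 < ΔC < λΔE. With the plan's expected differences used purely as illustration, that band runs from 0 to 0.15λ at the smaller difference and from 0 to 0.28λ at the larger. The rules coincide in general only if ΔE = 0.

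**2. Hospice coverage**

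- WSIC cost sectors (Table 1): primary care, acute, community, mental health, social care.
- WSIC coded data (Table 1): primary, secondary, acute, mental health, community health, social care.
- Hospice is named in neither list. Table 1 does name hospices as sources for the CMC records and for Leeds. However, CMC records exist only for the EPaCCS group, so they cannot supply hospice use for controls, and Leeds is not a data source for 2B.
- The utilisation-times-unit-cost route picks up hospice care only if the data record hospice use.

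Suppose hospice were wholly uncosted. Let s be the share of displaced hospital deaths that go to hospice, and r the hospice cost divided by the hospital cost avoided. Then true saving ÷ apparent saving = 1 − s × r. Both inputs are assumed:

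| s | r | true ÷ apparent |
|---|---|---|
| 0.25 | 0.5 | 1 − 0.125 = 0.875 |
| 0.25 | 1 | 1 − 0.25 = 0.75 |
| 0.5 | 1 | 1 − 0.5 = 0.50 |
| 1 | 1 | 1 − 1 = 0 |

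**The case against.** The best defence has four parts.

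- **Objective 2B is modest.** It asks only about the effect on healthcare costs, and the planned cost modelling can answer that. Since 2A estimates outcomes in the same linked data, it would be wrong to say that the economic work has no effect measure. If costs fall and outcomes improve, the two results side by side would point to better cost-effectiveness. This stands, but it covers only that one case and gives no joint uncertainty. It does not reconcile the cost-minimisation label with the stated hypothesis.
- **Hospice may be costed after all.** A reader might infer that a hospital-to-hospice shift would be booked as a pure saving and that the result must favour EPaCCS. The document does not support that. Hospice spend could sit within the community sector, the unit-cost route neither names nor excludes it, and place of death is held in WSIC, so hospice deaths may be identifiable. Informal care and intervention costs are also added, so the net direction of any bias cannot be fixed from the text.
- **Informal care.** Using literature-based hours goes beyond the healthcare-cost wording of 2B. The source is declared and the valuation method has a primary and a sensitivity version, so this is a minor scope mismatch and not an error.
- **Detail belongs in the analysis plan.** A full statistical analysis plan is promised, and cost lines or bootstrap details could properly appear there. That covers the details. It does not cover a named method that conflicts with a named hypothesis in the article itself.

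**Conclusion.** The concern holds in two parts of unequal strength. The conflict between cost minimisation and the outcome and cost-effectiveness hypotheses is plain in the text and needs no assumption. As written, the cost-effectiveness hypothesis cannot be tested.

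The hospice part is a gap to be clarified. Savings may be overstated if WSIC does not capture hospice care, by an amount that depends on s and r, neither of which the article gives. The tabulated ratios are illustrations that assume no hospice costing at all; they do not estimate the error in the study. Displaced deaths may also occur at home or elsewhere, which lowers s. The primary outcome, place of death, is unaffected; what is at stake is the economic conclusion.

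**What to change.** Choose one of two routes for the main point:

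1. Replace the cost-minimisation label with a cost-consequence analysis, and report incremental cost per hospital death avoided from the same weighted North West London cohort. The denominator needs a weighted risk difference in addition to the planned marginal odds ratios. Bootstrap patients, re-estimating the weights in each resample, and compute both differences together so that uncertainty is joint.
2. Withdraw the cost-effectiveness hypothesis and limit 2B to a cost comparison.

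Under either route, confirm whether WSIC totals capture hospice care. If they do not, add a hospice cost for hospice deaths in both groups over a stated range of length of stay and unit cost. Otherwise, state that totals exclude hospice and claim no overall saving.

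The cost is some rewording, one extra cost line if hospice is missing, and a bootstrap under the first route. No new cohort is needed. The downside is a possibly less favourable and more uncertain cost result.
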